### Digital intervention development and description

The digital app, My Sugar Journey (Fig. 3), has been developed for use in South Asian Indian states (both in urban and rural areas) namely; from northern India Delhi and southern India Tamil Nadu (Chennai urban and Chunampet rural). Building on the lessons learned from the pilot study [12], we ensured that the app was also available in the local language commonly spoken in the two states. The development process involved careful consideration of regional factors and user preferences. The outcomes of the initial testing helped refine the app’s features for better usability and relevance.

**Fig. 3 Fig3:**
[figure not shown]
The digital intervention app, My Sugar Journey

In the beta testing phase, a total of 25 individuals from diverse backgrounds tested the app. The group included scientists, doctors, managers, diabetes educators, app developers, freelancers, illustrators and home makers, as well as some people with diabetes. This varied tester profile allowed us to gather valuable feedback from different professional perspectives, which was instrumental in fine-tuning the app for a wide range of users.

The app is available in three languages: English, Hindi and Tamil. The software is implemented as a mobile phone application and is available for download within research settings from the Google Play Store and the Apple App Store for Android and iPhone users, respectively. Once the recruited participant downloads the MSJ application, the study team sends a study code to register and use the app.

The main functionalities of the MSJ app include: (i) browsing lifestyle and behavioural suggestions, including nutrition and meal planning through recipes (ii) an artificial intelligence (AI) enabled chat-bot helping participants to navigate through various lifestyle sections (iii) gamification with each gaming level providing lifestyle and behavioural advice (iv) self-monitoring of selected behaviours (step-count, physical activity and food tracking, as well as weight tracking), (v) getting prompts and summary feedback for habit formation through push-notifications, and (vi) a brief quiz based on the content given in the app to enhance engagement.

Lifestyle goals of the intervention are to improve diet, increase physical activity, reduce sedentary behaviour, reduce excess body weight, improve sleep, reduce stress, cease (or at least decrease) smoking, and moderate alcohol consumption. The targets for diet and lifestyle are based on the American Diabetes Association recommendations [23].

Participants enrolled in the digital intervention arm receive once monthly telephone calls for the 6 months intervention (a maximum of 6 telephone calls in total), only if there is no engagement with the app over any particular month. App engagement will be monitored based on app usage from the backend data team. During the telephone call, participants are simply asked if any technical issues and gently prompted to use the app. The anticipated duration of the telephone call is approximately 1–2 min. From our pilot data conducted during the Covid-19 period [12], there was a relatively high dropout rate, and hence engagement telephone calls have been incorporated. Research personnel making telephone calls do not need specific training in diabetes or dietetics, as the objective is to serve as a reminder to participants to engage with the app, keeping the support cost-effective and accessible.

### Primary and secondary outcomes

The primary outcome is incidence of T2D at 24 months (as determined by the specific criterion applied to each individual on their admission into the study (fasting glucose, 2-hour glucose on OGTT, and/or HbA1c). For example, if an individual’s prediabetes status was defined by HbA1c value (within the range 42-47mmol/mol), their progression to type 2 diabetes will be defined by the associated HbA1c threshold (48mmol/mol or greater). Changes over 6 and 12 months are considered secondary outcomes.

Secondary outcomes are listed in Table 1 and include changes in cardiometabolic outcomes; intervention uptake, use and satisfaction; behavioural and clinical outcomes; and costs related to implementation. Data will be collected at baseline, and 6, 12 and 24 months as outlined in Table 1.

### Qualitative outcomes

Between 6 and 12 months into the study, focus group discussions will be conducted with up to 15 participants from both urban and rural areas of Chennai and Delhi. Interviewees will be selected through purposive sampling, aiming for variation across geographical area, socioeconomic background and areas of high and low uptake. The aim is to explore the challenges and barriers associated with using digital interventions for lifestyle behaviour modification among individuals living in South Asia. Semi-structured interviews will be conducted using pre-designed guides by trained interviewers.

### Statistics and data analysis

The primary analyses will be based on an intention to treat (ITT) principle. All participants who are randomised into the study will be included in the ITT analysis and the analysis is conducted according to the randomised treatment arm. Outcomes will be assessed for normal distribution.

For the primary outcome, the incidence of T2D in each study arm will be determined based on the participants’ entry criterion. Change in HbA1c, fasting glucose, or 2-hour OGTT glucose values will be calculated from baseline to endpoint (at 12 months and 24months) and reported based on the specific criterion applied to each individual on their admission into the study. Outcomes will be assessed by two-tailed unpaired t-test if normally distributed or the Wilcoxon Rank sum test if non-normally distributed.

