### Sample size and feasibility

Based on our previous findings, the expected diabetes risk reduction based on previous face to face prevention studies has been shown to be 28–32%. We hypothesized that a digital intervention would enable a 24% reduction in the incidence of T2D (*p* < 0.05) compared to the control group. The effect size selected was based on published literature which suggests lower effectiveness for digital compared to face-face interventions.

To demonstrate that difference as significant at *p* < 0.05 and with 80% power and accounting for approximately 20% drop-out rate, 3,240 participants will be recruited.

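### The endpoint-by-endpoint two-sample tests make no use of 6- and 12-month values for people missing at 24 months; a cluster-aware repeated-measures model suits the secondary continuous outcomes better

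*Protocol article*

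**What the plan says.** The section *Statistics and data analysis* deals with change in HbA1c, fasting glucose and 2-hour glucose, which "will be calculated from baseline to endpoint (at 12 months and 24months"), reported by each person's entry criterion. It then gives a general rule: "Outcomes will be assessed by two-tailed unpaired t-test if normally distributed or the Wilcoxon Rank sum test if non-normally distributed". The same section states that "All participants who are randomised into the study will be included in the ITT analysis".

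*Primary and secondary outcomes* says "Data will be collected at baseline, and 6, 12 and 24 months as outlined in Table 1" and "Changes over 6 and 12 months are considered secondary outcomes". Table 1 marks HbA1c and the capillary OGTT at baseline, 12 and 24 months. It marks anthropometrics, blood pressure, food frequency, physical activity and EQ-5D at baseline, 6, 12 and 24 months.

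The sample size is set "accounting for approximately 20% drop-out rate". Of the pilot, *Digital intervention development and description* reports that "there was a relatively high dropout rate, and hence engagement telephone calls have been incorporated".

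**The concern.** The article does not leave the method open. It names a two-sample test on change to an endpoint. Run on observed values, that test can use only people seen at that visit, so someone measured at 6 and 12 months but absent at 24 contributes nothing to the 24-month comparison.

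Two things are at stake. The first is precision, because information that has been collected goes unused. The second is bias. If poor early responders leave the app arm more readily than comparable controls, the app-arm people who remain at 24 months look better than the arm as randomised, and the secondary effects are overstated. If good early responders leave more readily, the error runs the other way.

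The named tests also do not by themselves deliver the stated inclusion of everyone randomised.

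**Working it through.** **How many people.** The design has 90 clusters × 36 = 3,240, which matches the stated total. Twenty per cent of 3,240 is 648, leaving 2,592, or 1,296 per arm.

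**Weight (three follow-up visits).** The documents give no variances, correlations or drop-out mechanism, so all of these are assumptions:
- SD of change: 3, 3.5 and 4 kg at 6, 12 and 24 months.
- Correlations: 0.75 (6-12), 0.60 (6-24) and 0.75 (12-24).
- About 20% lost by month 24 in each arm, 1,620 randomised per arm, no cluster effect, true effect zero.
- The log-odds of leaving rise with the last observed weight change, by the slope per kg shown below.

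Simulation results for the unpaired comparison at 24 months:

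| Slope, app arm | Slope, control arm | Bias (kg) | False positives |
|---|---|---|---|
| 0 | 0 | 0.00 | nominal |
| 0.15 | 0.15 | 0.00 | 5% |
| 0.30 | 0.30 | 0.00 | 5% |
| 0.15 | 0.075 | -0.14 | about 14% |
| 0.30 | 0.15 | -0.23 | 30-32% |
| 0.15 | 0 | -0.28 | 42% |
| 0.30 | 0 | -0.47 to -0.49 | 86-88% |

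The ranges are differences between repeat runs. With correlations of 0.70, 0.50 and 0.70, the last two biases are -0.25 kg and -0.43 to -0.45 kg.

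**Check by formula.** The standard error at 24 months is √(4²/1,296 + 4²/1,296) = 0.157 kg. The false-positive rate is close to P(Z > 1.96 − |bias|/SE), plus a negligible far tail:
- Bias 0.14: 0.14/0.157 = 0.89, so P(Z > 1.07) ≈ 14%.
- Bias 0.23: 0.23/0.157 = 1.46, so P(Z > 0.50) ≈ 31%.
- Bias 0.28: 0.28/0.157 = 1.78, so P(Z > 0.18) ≈ 43%.

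These agree with the simulation.

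**A likelihood estimate that uses all visits**, on the same data, has bias within 0.01 kg. Under random drop-out its standard error is 0.150 against 0.157, and 1 − 0.150/0.157 ≈ 4%.

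**HbA1c and glucose (12 and 24 months only).** This check is in SD units, with 20% missing at 24 months, log-odds of leaving 0.7 per SD of 12-month change, and 12-24 month correlation 0.3 / 0.5 / 0.7 (all assumed).
- Dependence in the app arm only, no true effect: bias -0.04 / -0.065 / -0.09. With SE = √(2/1,296) = 0.039, the error rate is about 17% / 38% / 65%.
- Same rule in both arms, no true effect: no bias.
- Same rule in both arms, true effect -0.20: bias 0.004 to 0.01 towards zero.
- Leaving unrelated to response: no bias.

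Because glycaemic changes are reported by entry criterion, each measure may be analysed in fewer than 1,296 per arm. The biases would be unchanged, but the error rates would be lower.

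**The case against.** **The plan may not discard anything.** The statement that all randomised participants are included needs some way of filling missing values, and a t-test can be run on data imputed from the 6- and 12-month visits. The method may stand in an analysis plan that is not shown. A reader might infer that the trial is committed to a completers-only analysis; the article does not say so. What stands is narrower: the test it names makes no use of earlier visits unless something is added to it.

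**Dependence on response is not enough for bias.** A reader might infer that the test is valid only if leaving is unrelated to how people are doing. The table contradicts this: equal dependence in both arms gives no bias under the null. The largest figures need app-arm leaving to follow response while control leaving does not, which is an extreme case.

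**The evidence for arm-specific loss is weak.** Abandoning the app is not missing a study visit. The pilot ran during the Covid-19 period, and the article gives no rate, arm split or link to response. It does show that only the app arm has an app to abandon and reminder calls triggered by non-use. That makes different patterns of leaving possible, not established.

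**The comparison favours the alternative.** Drop-out was generated from observed values, which is exactly what the mixed model assumes. Leaving driven by unobserved values was not tested.

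**The article allows a rank test for non-normal outcomes.** A normal-theory model would drop that provision, so the fix has to replace it. This objection is accepted.

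**Conclusion.** The point holds as an improvement to a stated method for the secondary continuous outcomes. The named tests set aside scheduled measurements for up to about 648 people unless imputation is added. The sure cost is small, about 4% in standard error on the assumed correlations. The possible cost is larger but conditional: for weight about -0.14 to -0.23 kg with 14-32% false positives if the app-arm dependence is twice that in controls, up to about -0.47 kg in the one-sided extreme, and essentially nothing under the null if the arms behave alike. Every slope, SD and correlation behind these figures is an assumption.

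The glycaemic sentence covers 12 and 24 months only. The three-visit outcomes come under the general test sentence together with Table 1. A reader might extend the concern to the main result, but "The primary outcome is incidence of T2D at 24 months", which is binary and not affected by this point. The simulations set the cluster effect to zero; that the named tests ignore cluster randomisation is a separate matter.

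**What to change.** For each continuous outcome measured at more than one follow-up visit, replace the separate two-sample tests with one mixed model for repeated measures:
- all scheduled follow-up visits as responses (12 and 24 months for HbA1c and glucose; 6, 12 and 24 months for the others);
- baseline value, visit and arm-by-visit terms;
- unstructured within-person covariance;
- a random effect for the randomised cluster.

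Read the arm difference at each visit, with its confidence interval, from that model. For clearly skewed outcomes, in place of the rank sum test, transform the outcome or use robust or bootstrap standard errors that respect the clusters. Say how the model serves the statement that all randomised participants are included.

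The cost is analysis wording and modest programming, with no new data or visits. Recruitment is described as ongoing, so the change can still be made before outcome data are analysed. The model assumes that missingness is explained by observed values. It does not cover leaving that depends on unobserved values, and it gains nothing from people with no follow-up value at all.

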### Participant screening

Participants will be identified through a targeted screening process conducted by the field team. During these visits, the research team will assess potential individuals based on the study’s preliminary inclusion criteria. Prior to participating in any study-specific screening activities, potential participants will be required to sign the approved informed consent form. Eligibility will be assessed through screening evaluations, and reasons for any exclusions will be recorded in a Participant Screening Log.

The study screening procedures are summarised in Fig. 1.

#### Screening STEP 1

During the first screening visit, eligibility will be evaluated based on the inclusion and exclusion criteria, the IDRS score, and random capillary blood glucose [13].

Participants meeting the criteria – defined as IDRS ≥ 30 and/or a random capillary blood glucose level ≥ 110 mg/dL – will proceed to the second stage of screening. In Asian Indians, a screening threshold of random capillary blood glucose ≥ 110 mg/dL is recommended [17].

#### Screening STEP 2

In this stage, a capillary oral glucose tolerance test (OGTT) [18, 19] will be performed and venous blood samples collected to measure HbA1c and haemoglobin levels. Additionally, anthropometric measurements, including blood pressure, height, weight, waist circumference, and body composition, will be recorded. Participants will also complete assessments related to quality of life (QOL-Eq. 5D), sleep patterns, alcohol use, smoking status, and socioeconomic status, the latter of which will be evaluated using a standardized scale relevant to India that considers occupation, income, and education – the Kuppuswamy Scale [20].

Participants meeting the inclusion criteria will be enrolled on to the study. For individuals with a haemoglobin less than 10 g/L, the HbA1c value will be disregarded, due to anaemia affecting glycated haemoglobin [21, 22]). In people with haemoglobin < 10 g/L, inclusion criteria will solely be dependent on the fasting glucose or 2-hour post-OGTT glucose. Participants diagnosed with T2D will be directed for specific diabetes care in local healthcare centres.

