### Study intervention

A description of activities at each visit has been outlined below and a summary provided in Table 1.

**Table 1 Tab1:** Quantitative outcome measures

Outcome measures	Baseline	Month 6	Month 12	Month 24
Demographics	X			
Anthropometrics (height, body weight, waist circumference, BMI)	X	X	X	X
HbA1c	X		X	X
Capillary oral glucose tolerance test	X		X	X
Systolic and diastolic blood pressure	X	X	X	X
Food frequency questionnaire	X	X	X	X
Physical activity – MPAQ questionnaire	X	X	X	X
Lifestyle questionnaire - smoking, alcohol	X	X	X	X
Socioeconomic status tool	X			X
App engagement and usage outcomes^a^				
Total time spent per participant on app per day/week/month/entire duration	X	X		
App session interval (i.e. time between visits to the app)	X	X		
Number of sessions per participant on app per day/week/month/entire duration	X	X		
MARS questionnaire (for intervention group only)		X		
Economic outcomes				
QOL-EQ -5D	X	X	X	X
Collection of hospital care and associated costs	X	X	X	X

^a^For intervention group only

Abbreviations: *BMI*, body mass index; *HbA1c*, glycated haemoglobin; *MARS*, mobile application rating scale; *MPAQ*, Madras diabetes research Foundation - Physical activity questionnaire; *QOL-EQ-5D*, quality of life EuroQol Group-5D questionnaire

After randomization, study participants will receive instructions on how to proceed in the study according to their study group. Individuals in the control group will receive an educational session, either via telephone or will be directed to a local healthcare clinic. Standard educational materials will be provided on lifestyle risk factors of T2D and recommendations on a healthy diet and physical activity in accordance with international and national recommendations.

For participants assigned to the digital intervention group, the research team will conduct home visits to administer study questionnaires, assist with downloading the digital intervention app, and complete the onboarding process. During this visit, participants will receive a brief overview of the app’s functionality and features.

After the 6-month intervention period, participants will continue to have access to the digital app on their phones and may use it at their discretion. However, no further active engagement will be provided, such as notifications, nudges, or telephone calls. Participants are free to interact with the app’s features as they wish.

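### Glycaemic change is planned as an unadjusted change score reported by entry criterion, although HbA1c and OGTT are scheduled for everyone; this costs precision and leaves each effect estimated in selected subsets

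*Protocol article*

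**What the plan says.** Statistics and data analysis defines the glycaemic change outcome: "Change in HbA1c, fasting glucose, or 2-hour OGTT glucose values will be calculated from baseline to endpoint (at 12 months and 24months"). In the same sentence it is to be "reported based on the specific criterion applied to each individual on their admission into the study". The test follows: "Outcomes will be assessed by two-tailed unpaired t-test if normally distributed or the Wilcoxon Rank sum test if non-normally distributed". No baseline covariate is mentioned.

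The same section states the analysis population: "All participants who are randomised into the study will be included in the ITT analysis".

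The measurements are not tied to the entry criterion:

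- Under Participant screening (Screening STEP 2), a capillary OGTT "will be performed and venous blood samples collected to measure HbA1c and haemoglobin levels".
- Table 1 (Study intervention) lists HbA1c and "Capillary oral glucose tolerance test" at baseline, month 12 and month 24.
- Primary and secondary outcomes points to that schedule: "Data will be collected at baseline, and 6, 12 and 24 months as outlined in Table 1".

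The one stated reason to set a value aside is HbA1c in participants below the haemoglobin cut-off (Screening STEP 2).

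**The concern.** For the primary endpoint, each person is judged on the measure that admitted them. The analysis section carries the same phrase over to continuous change. Read that way, an HbA1c reading from someone admitted on 2-hour glucose is collected three times and not used in the HbA1c comparison.

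Three things are at stake.

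- **Precision.** Fewer participants contribute to each measure, and the available baseline value is not used as a covariate.
- **Population.** The app's effect on HbA1c or on glucose is estimated in people selected on that same reading. The subsets overlap, because the inclusion criteria are joined by and/or. This sits uneasily with the statement that all randomised participants are analysed.
- **Interpretation.** Each subset was chosen because that reading lay in a raised band (for HbA1c, 42-47 mmol/mol). Part of any fall within an arm is therefore regression to the mean and could be misread as improvement.

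**Working it through.** **The plan's own figures.** The article gives no sample size, SD or power for glycaemic change, so there is no figure of that kind to reproduce. The overall total does agree with the cluster layout: (60 + 30) clusters x 36 = 3,240.

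**Inputs from the article.** N = 3,240, about 20% drop-out, 90 clusters of 36. Evaluable participants: 3,240 x 0.8 = 2,592, which is m = 36 x 0.8 = 28.8 per cluster.

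**Assumed inputs, because the article gives none.** These are the share f entering on a given measure, the ICC, the baseline to follow-up correlation r, and the ratio k of baseline SD to follow-up SD. The share is taken as equal across clusters, and the outcome variance as the same in the subset and the full sample.

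**Step 1: restriction to the entry criterion.** The variance of the arm difference is proportional to (1 + (n - 1) x ICC) / n, with n evaluable per cluster. Hence

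SE inflation = sqrt{ [1 + (m f - 1) ICC] / ( f [1 + (m - 1) ICC] ) }.

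Example, f = 0.33 and ICC = 0.05: m f = 9.504. The numerator is 1 + 8.504 x 0.05 = 1.425. The denominator is 0.33 x (1 + 27.8 x 0.05) = 0.33 x 2.39 = 0.789. The ratio is 1.81 and its square root 1.34.

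| Share f | Used | Not used | ICC 0 | ICC 0.02 | ICC 0.05 |
|---|---|---|---|---|---|
| 0.20 | 518 | 2,074 | 2.24 | 1.88 | 1.61 |
| 0.33 | 855 | 1,737 | 1.74 | 1.51 | 1.34 |
| 0.50 | 1,296 | 1,296 | 1.41 | 1.28 | 1.18 |
| 0.70 | 1,814 | 778 | 1.20 | 1.13 | 1.08 |

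If everyone qualifies on at least one of three measures, the three shares sum to at least 1 and average at least one third. A single measure may lie below that.

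**Step 2: change score against baseline adjustment.** Variance ratio, adjusted to change score = (1 - r^2) / (1 + k^2 - 2 k r). With k = 1 this is (1 + r)/2:

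- r = 0.3: 0.65 (SE 19% smaller)
- r = 0.5: 0.75 (SE 13% smaller)
- r = 0.7: 0.85 (SE 8% smaller)

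A narrow entry band shrinks the baseline SD. With k = 0.4:

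- r = 0.2: 0.96 / 1.00 = 0.96
- r = 0.4: 0.84 / 0.84 = 1.00
- r = 0.6: 0.64 / 0.68 = 0.94

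Within an entry subset, adjustment may therefore gain little.

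**Step 3: bias between arms.** By the caption of Fig. 1, the two screening steps come before recruitment and randomisation. Entry criterion and baseline value therefore precede the intervention, and regression to the mean acts on both arms alike.

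**The case against.** **The word only is not in the text.** The article says how change is reported; it does not say that other readings are excluded. The sentence stands in a paragraph that opens with the primary outcome. Primary and secondary outcomes makes the Table 1 measures secondary outcomes, and Table 1 carries no restriction. This stands in part: restriction is the natural reading but not the only possible one. If the sponsor means something else, the sentence still needs rewriting.

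**A change score is valid under randomisation, and covariates are often left to the analysis plan.** The first half stands: the issue is efficiency, not validity. The second half has less force, because the article itself fixes both the change score and the unadjusted test.

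**The loss may be small.** This stands as a limit on size. Overlapping entry makes one third a floor for the average share. At a 70% share and ICC 0.05 the inflation is only 1.08.

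**HbA1c should not be analysed in literally everyone.** This stands. The low-haemoglobin rule is a stated reason for omission, and the remedy must keep it.

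**Conclusion.** The point holds as a loss of precision and of the randomised population for the continuous glycaemic outcomes. It does not touch the definition of the primary incidence endpoint. Under the assumed shares of 20-70%, the restriction inflates the standard error 1.20-2.24 times at ICC 0 and 1.08-1.61 times at ICC 0.05. It costs precision in every scenario shown. Most of the loss comes from the restriction; the gain from baseline adjustment depends on assumptions and may be near nil within a narrow entry band.

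A reader might infer more, and the documents do not support it:

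- **That the treatment comparison is biased.** Selection and baseline precede the intervention, so it is not. Regression to the mean affects the within-arm changes.
- **That most of the sample is lost for every measure.** This needs a share below one half on each. The shares are not given, and entry criteria can overlap.
- **That no estimate in the randomised population will exist.** The wording does not rule out a further analysis in everyone.
- **That the standard error could be halved.** One third x 0.75 = 0.25 in variance gives that result, but only with equal SDs and no clustering. At a one-third share, ICC 0.05 and a variance ratio of 0.94-1.00, the full-sample SE is sqrt(0.94)/1.34 = 0.72 to 1/1.34 = 0.75 of the subset SE.

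That the unpaired test ignores cluster randomisation is a separate and larger matter, and adds no weight here.

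**What to change.** In Statistics and data analysis, state that HbA1c, fasting glucose and 2-hour glucose at 12 and 24 months are each analysed in all randomised participants with usable data, whatever their entry criterion, keeping the Screening STEP 2 rule on HbA1c at low haemoglobin. Use a model with the baseline value of that measure as covariate and a term for cluster. Show results by entry criterion as supportive subgroups, with a note that within-arm changes in them include regression to the mean.

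The cost is a change of wording. The measurements are already scheduled, no visit or assay is added, and the article reports recruitment as ongoing, so the change can be made before analysis.

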## Methods/design

### Design

This is a cluster randomised, parallel group prospective study comparing the digital intervention group (Intervention group) and control group receiving usual care (Control group). (Fig. 1). A total of 3,240 participants will be recruited over 2 years from Delhi in the north (urban and rural) and Tamil Nadu (urban-Chennai and rural-Chunampet) in the south of India.

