### Participant recruitment and cluster randomisation

Participants will be cluster randomised from both urban and rural areas across Tamil Nadu and Delhi (Fig. 2). Using STATA software, clusters will be randomly allocated in a 1:1 ratio to either the control group, which will receive the standard of care, or the intervention group, which will receive the digital intervention.

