**Fig. 2 Fig2:**
[figure not shown]
Summary of participant and cluster recruitment in urban and rural Chennai and Delhi. A total of 60 clusters (30 urban and 30 rural) will be recruited in Chennai, with 30 clusters (15 urban and 15 rural) in Delhi. Each cluster represents 36 participants to be recruited

In Tamil Nadu, a total of 60 clusters (30 urban and 30 rural) will be established to recruit 2,160 participants (Fig. 2). The Chennai city (urban) has 200 wards, with 68 wards having a population density greater than 10,000. Each urban ward will constitute a single cluster, with 36 participants recruited per cluster. In rural areas, three villages will be grouped together to form one cluster to achieve the target of 36 participants per cluster. This approach accounts for the anticipated lower prevalence of prediabetes in rural areas compared to urban settings, requiring more extensive screening to meet the cluster size.

Similarly, in Delhi, a total of 30 clusters (15 urban and 15 rural) will be recruited. Delhi’s urban population is organized into blocks, while the rural population is divided into clusters. The study will screen 15 urban clusters (2 or 3 blocks will be combined to form a cluster) with a population density of 29,638 and 15 rural clusters with a population density of 29,434. Both in urban and rural areas, participants will be screened till the target of 36 participants per cluster is achieved.

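### The only tests named, an unpaired t-test and a Wilcoxon rank sum test on participants, ignore the 90 randomised clusters, so the 5% error rate is not held

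*Protocol article*

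**What the plan says.** The Design section states the design plainly: "This is a cluster randomised, parallel group prospective study". The section Participant recruitment and cluster randomisation says that "clusters will be randomly allocated in a 1:1 ratio to either the control group" or to the intervention group. The legend of Fig. 2 gives the numbers: "A total of 60 clusters (30 urban and 30 rural) will be recruited in Chennai, with 30 clusters (15 urban and 15 rural) in Delhi". It adds: "Each cluster represents 36 participants to be recruited".

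Sample size and feasibility sets the error rate and power ("To demonstrate that difference as significant at *p* < 0.05 and with 80% power") for the hypothesis that "a digital intervention would enable a 24% reduction in the incidence of T2D". It states no control-arm incidence, ICC or design effect.

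Statistics and data analysis covers all randomised participants by intention to treat and describes changes in each participant's glucose or HbA1c. The paragraph that opens with the primary outcome ends with the only tests named anywhere in the article: "Outcomes will be assessed by two-tailed unpaired t-test if normally distributed or the Wilcoxon Rank sum test if non-normally distributed".

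**The concern.** The unit of randomisation is a place; the unit in the analysis text is a person. An unpaired t-test and a rank sum test both take every observation as independent. That is doubtful for people recruited from one ward or one group of villages. The Discussion itself justifies clustering by how closely members of rural communities are connected, although the Methods randomise clusters in urban areas too.

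If outcomes within a cluster are positively correlated, the arm difference varies more than these tests assume. P-values are then too small, and any confidence interval built on the same standard error is too narrow. A significant result on diabetes incidence could be challenged as a product of ignored clustering. A change of method after the results are known would look post hoc.

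**Working it through.** **Inputs from the article**
- Clusters: 60 + 30 = 90, so 45 per arm at 1:1 (Fig. 2 legend).
- Cluster size: 36 recruited (Fig. 2 legend). With about 20% drop-out (Sample size and feasibility), 36 × 0.8 = 28.8 evaluable.
- Nominal two-sided level: 5%.

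**Not in the article, assumed here**
- ICC: 0.001 to 0.10.
- Incidence of 20% in both arms, used only to simulate a binary outcome under the null.

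**The article's own figure.** 90 × 36 = 3,240 (2,160 in Tamil Nadu and 1,080 in Delhi), which matches the stated total. The power statement cannot be reproduced, because control incidence and ICC are not given.

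**Formulas.** With m participants per cluster, the design effect is DE = 1 + (m − 1) × ICC. A test that ignores clusters understates the standard error by a factor √DE. Its true two-sided error is therefore 2 × [1 − Φ(1.96/√DE)].

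Worked example at m = 28.8 and ICC 0.02: DE = 1 + 27.8 × 0.02 = 1.556; √DE = 1.247; 1.96/1.247 = 1.571; true error = 11.6%.

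| ICC (assumed) | DE, m = 28.8 | True error, m = 28.8 | True error, m = 36 |
|---|---|---|---|
| 0.001 | 1.03 | 5.3% | 5.4% |
| 0.005 | 1.14 | 6.6% | 7.1% |
| 0.01 | 1.28 | 8.3% | 9.2% |
| 0.02 | 1.56 | 11.6% | 13.3% |
| 0.03 | 1.83 | 14.8% | 17.1% |
| 0.05 | 2.39 | 20.5% | 23.7% |
| 0.10 | 3.78 | 31.3% | 35.6% |

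**Check by simulation under the null.** 4,000 trials, 45 clusters per arm, 29 participants per cluster. The Monte Carlo standard error near 5% is √(0.05 × 0.95/4,000) ≈ 0.3 percentage points.

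| ICC | t-test on participants | Wilcoxon on participants | Two-proportion test on participants (20% incidence) | t-test on cluster means |
|---|---|---|---|---|
| 0 | 4.9% | 4.9% | 5.2% | 5.0% |
| 0.01 | 8.9% | 8.4% | 8.8% | 5.4% |
| 0.02 | 11.9% | 11.6% | 11.8% | 5.3% |
| 0.05 | 20.5% | 20.0% | 19.9% | 5.0% |

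A separate simulation of a binary outcome (20,000 runs, 20% incidence) agrees. The participant-level test rejected 8.5%, 11.5% and 21.1% of null trials at ICC 0.01, 0.02 and 0.05; the t-test on cluster-level summaries rejected 5.0%, 4.9% and 5.0%.

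**The case against.** - **The unit of analysis is never stated in so many words.** A t-test on cluster means is itself valid, so the named test is not wrong in every reading. But the surrounding text speaks of randomised participants and individual values, and nothing points to cluster summaries. The participant-level reading is the natural one.
- **A condensed article may leave cluster adjustment to a statistical analysis plan that is not shown.** Silence on the method would indeed be no finding. Here the article names specific tests that do not fit its own design. If another document specifies a cluster-adjusted analysis, the two conflict and must be reconciled.
- **The normality condition fits continuous changes, not the binary primary outcome.** This is fair: neither named test suits incidence of diabetes, which is a separate weakness. It does not rescue the primary analysis, since an unadjusted comparison of proportions inflates the error to the same degree.
- **Not every secondary outcome is affected.** This stands. App use and the app rating questionnaire are collected in the intervention group only (Table 1), so they have no between-arm test. The article also mentions no confidence intervals; that consequence follows only if they are reported from the same standard errors.
- **The size depends on an ICC nobody has stated.** This stands too. At ICC 0 there is no inflation, and at 0.001 it is trivial. The direction, however, is fixed for any positive ICC.
- **28.8 per cluster does not match an analysis of all randomised participants.** Using 36 makes the inflation larger.

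**Conclusion.** The concern holds. The analysis sentence, read as the section reads, contradicts the cluster design and does not control the type I error at 5%. Over an assumed ICC of 0.01 to 0.05 with 28.8 evaluable per cluster, the true error is about 8% to 20%, and it already reaches 6.6% at ICC 0.005. The conclusion rests on participant-level use of the named tests and on a positive ICC; only the size of the excess, not its direction, depends on the ICC value. It covers the primary outcome and every secondary outcome compared between arms. This must be corrected before the analysis.

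**What to change.** Replace the sentence with an analysis that accounts for the randomised cluster, defined as the ward, combined blocks or village group. Either of these would do:
- a mixed-effects model or GEE with cluster as the grouping unit, in a binary form for diabetes incidence and a linear form for continuous changes; or
- an unpaired t-test on the 90 cluster summaries (proportions or means), with 90 − 2 = 88 degrees of freedom.

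Apply it to the primary outcome and to every secondary between-arm comparison. A small-sample correction for the model-based option (45 clusters per arm) and a report of the observed ICC are good practice. If an analysis plan already specifies such a method, bring the article into line with it.

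The cost is wording only: no new data or participants. The Ethics approval section says recruitment is ongoing, so the correction can still be dated before the results are known. Correct standard errors will be larger by √DE: about 13%, 25% and 55% at ICC 0.01, 0.02 and 0.05.

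The power claim should be checked at the same time. With 3,240 × 0.8 = 2,592 evaluable, 80% power for a 24% relative reduction needs a control incidence of about 15.9% at ICC 0, 19.6% at 0.01, 23.0% at 0.02 and 31.8% at 0.05. The assumed incidence and ICC should therefore be stated.
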